#### Statistical analysis

2.7.2

The primary analysis will be based on participants' randomization assignment regardless of their achieved BP levels (intention‐to‐treat analysis). Follow‐up time will be calculated from the date of randomization to the date of the event ascertainment for patients with event occurrence, the date of the trial completion for patients without event occurrence, the date of death for patients who died during follow‐up, or the date of last contact for patients lost to follow‐up. Cox proportional hazards regression will be used to compare the time from randomization to the first CVD event between the randomization groups with two‐sided tests at the 5% level of significance. The model will include an indicator for intervention as its sole predictor variable. Study center at randomization will be a stratifying factor.

Tests of secondary outcomes will be conducted with models similar to those used in the primary analysis. These will be reported with 95% CIs and nominal *p* values without an adjustment for multiple comparisons. Interactions between treatment effect and prespecified subgroups will be assessed with a likelihood‐ratio test using Hommel adjusted *p* values. The multiple imputation techniques will be used in the sensitivity analysis of the primary and secondary outcomes.

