### Outcomes

2.3

Occurrence of study outcomes will be collected every 3 months beginning at the 3‐month visit and throughout the follow‐up. The physician who collects outcome data is masked to treatment assignment. Photocopies of inpatient record, discharge summary, electrocardiogram, and imaging reports, etc. will be obtained for outcome adjudication by members of an outcome assessment committee who are unaware of treatment assignment. At least two committee members will review the medical records independently. Clinical events occurring during follow‐up will be ascertained equally in both treatment groups.

BPROAD study outcomes are listed in Table 2. The primary outcome for the BPROAD study is the composite end point of the first occurrence of nonfatal stroke, nonfatal myocardial infarction, hospitalized or treated heart failure, and cardiovascular death. The following subgroups are prespecified to test whether the effect of an intervention achieving systolic BP <120 mm Hg versus systolic BP <140 mm Hg on the primary study outcome is consistent in participants with different characteristics.Age at baseline (<65 vs ≥65 years; <80 vs ≥80 years).Men vs women.Systolic BP levels at baseline (tertiles).Previous CVD.Previous chronic kidney disease (CKD, estimated glomerular filtration rate [eGFR] <60 mL/min/1.73 m^2^).Glycated hemoglobin (HbA1c) at baseline (tertiles).Diabetes duration at baseline (< vs ≥ the median).High BP duration at baseline (< vs ≥ the median).

**TABLE 2 jdb13411-tbl-0002:** Study outcomes.

Primary outcome
Major adverse cardiovascular events defined as the composite endpoint of the first occurrence of nonfatal stroke, nonfatal MI, hospitalized or treated heart failure, and cardiovascular death.
B. Secondary outcomes

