### Data collection

2.5

Outcome data collection starts at 3 months after random assignment and every 3 months thereafter in both treatment groups. Participants in both treatment groups will be queried on the occurrence of study outcomes on the same schedule, which is every 3 months.

Assessments performed at the various visits include questionnaires, physical examinations, blood and urine collection, lab measurements, etc. (Table 3). The same schedule will be used for both randomization groups. Baseline characteristics include socio‐demographics, medical history, concomitant medications, anthropometrics, BP levels, fasting plasma glucose, HbA1c, laboratory chemistry, cognitive function, and health‐related quality of life measurements. BP will be measured based on the recommendations by the American Heart Association.^16^ Participants are advised to avoid cigarettes, alcohol, coffee/tea, and exercise for ≥30 min before BP measurements. BP is measured three times after 5 min of seated rest with 1‐min intervals between measurements, at the presence of observer. The automated device (Omron HEM‐907) will be used and one of three cuff sizes (pediatric, regular adult, or large) will be chosen on the basis of each participant's arm circumference. The mean of the three measurements will be used.

**TABLE 3 jdb13411-tbl-0003:** Measurement and data collection schedule.

	Bs/Rz	Month 3	Month 6	Month 9	Year 1 AV	Year 1 QV	Year 2 AV	Year 2 QV	Year 3 AV	Year 3 QV	Year 4 AV	Year 4 QV	Year 5 AV or close‐out
Questionnaires													
Medical history, SES variables	X												
Lifestyle factors	X						X				X		
Adherence and adverse events		X	X	X	X	X	X	X	X	X	X	X	X
Study outcomes		X	X	X	X	X	X	X	X	X	X	X	X
Physical examinations													
Seated BP, pulse and medication adjustment	X	X	X	X	X	X	X	X	X	X	X	X	X
Standing BP	X		X		X		X		X		X		X
Weight	X	X	X	X	X	X	X	X	X	X	X	X	X
Height	X												
Waist and hip circumference	X				X		X		X		X		X
ECG	X				X		X		X		X		X
Lab measurements													
Liver and kidney function, electrolytes, glucose^a^	X	X	X		X		X		X		X		X
Blood routine, 24‐h urinary electrolytes, protein, and creatinine excretion^a^	X				X		X		X		X		X
Serum creatinine, lipid profile, and HbA1c^b^	X				X		X		X		X		X
Urinary albumin and creatinine^b^	X				X		X		X		X		X
Cognitive function	X				X		X		X		X		X
Health related quality of life	X				X		X		X		X		X

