#### Sample size

2.7.1

The BPROAD study has a single primary outcome (composite major CVDs) and several key secondary outcomes. The sample size calculation is based on the primary outcome and use of the following assumptions:Event rate of composite major CVDs of 2.0% per year among patients in the standard treatment group20% effect size for the intervention (HR of 0.80)Two‐year uniform recruitment period and total study length of 5 years (defined by the time between randomization of the first participant and study closeout)2% per year loss to follow‐up rateTwo‐sided significance test at the 5% level, and a statistical power of 90%

Based on these assumptions, the BPROAD study will need to enroll a total of 12 702 patients with equal numbers in both treatment groups.

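### The primary Cox model is valid and adequately powered as planned, but it uses no patient-level prognostic covariate and so gives up a small amount of power

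*Protocol article*

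**What the plan says.** Section 2.7.2 (Statistical analysis) sets an intention-to-treat Cox regression of time to first event, tested two-sided at 5%. On the content of the model it says "The model will include an indicator for intervention as its sole predictor variable" and "Study center at randomization will be a stratifying factor". Center is also the only randomization stratum (section 2.6).

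The baseline data are rich. Section 2.5 (Data collection) lists "medical history, concomitant medications, anthropometrics, BP levels, fasting plasma glucose, HbA1c" among other items. Table 3 adds lifestyle factors and serum creatinine at baseline, and Table 1 uses smoking and eGFR as entry criteria. Section 2.3 (Outcomes) already names age, sex, baseline systolic BP, previous CVD, chronic kidney disease and HbA1c as subgroup factors.

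The sample size in section 2.7.1 rests on "Event rate of composite major CVDs of 2.0% per year among patients in the standard treatment group" and a hazard ratio of 0.80. It claims no gain from covariates.

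**The concern.** Entry runs from established cardiovascular disease, through subclinical disease, to risk factors alone, with no upper age limit. Baseline risk should therefore vary between patients, and variables likely to explain part of that variation are measured in everyone.

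The hazard ratio is non-collapsible. When prognostic covariates are left out, the treatment log hazard ratio sits closer to zero than the ratio conditional on them, while its standard error hardly changes. The treatment-only test then has less power than the adjusted test on the same events. What is at stake is a modest amount of power; neither the validity of the test nor the sample size is in question.

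**Working it through.** **Inputs from the article (section 2.7.1).** Control event rate 2.0% per year, HR 0.80, two-sided 5%, power 90%, 2-year uniform accrual, 5-year total length, 2% per year loss, 1:1 allocation.

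**Input that the article does not give.** The prognostic strength of the baseline variables. Assumed: one normal score with a log-hazard SD of 0.6 to 1.0. The first simulation below uses SDs from 0.5 to 1.25 (c-statistic about 0.64 to 0.80) to bracket this.

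**1. The plan's own figure.**
- Events (Schoenfeld): 4(1.960 + 1.282)² / (ln 0.80)² = 844.1, so 845.
- Event probability with exponential event and loss hazards, averaged over follow-up of 3 to 5 years:
  - control: 0.02/0.04 × [1 − (e^−0.12 − e^−0.20)/0.08] = 0.0738
  - intensive: 0.016/0.036 × [1 − (e^−0.108 − e^−0.18)/0.072] = 0.0595
  - mean: 0.06667
- N = 845/0.06667 = 12 675, against the stated 12 702 (0.2% apart). Freedman gives 12 780 and Lachin-Foulkes 12 763.
- At 12 702: 846.8 events; expected Z = √(846.8/4) × 0.2231 = 3.247; power Φ(3.247 − 1.960) = 90.1%.

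The unadjusted comparison therefore meets its target. This formula takes no account of the center strata.

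**2. Adjusted against unadjusted, no center strata.** N = 12 702, about 850 events, 800 simulated trials per setting, power taken from the mean Z. It matters which hazard ratio equals 0.80, so both cases are shown.

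| Score SD | Power if unadjusted HR is about 0.80: unadjusted → adjusted | Fewer patients for equal power | Power if conditional HR is 0.80: unadjusted → adjusted |
|---|---|---|---|
| 0.5 | 89.8% → 90.4% | 2% | 88.9% → 89.6% |
| 0.7 | 90.0% → 91.1% | 4% | 88.4% → 89.6% |
| 1.0 | 89.9% → 92.7% | 10% | 86.6% → 89.9% |
| 1.25 | 90.8% → 94.7% | 15% | 84.2% → 90.1% |

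The standard error was about 0.069 in both models. The gain comes from the log hazard ratio moving away from zero: at SD 1.0, an unadjusted HR of 0.7995 went with an adjusted 0.7895. The ratio of adjusted to unadjusted Z at SD 1.0 was 1.056 in both cases, so the relative gain does not depend on which hazard ratio is set to 0.80.

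**3. With center strata.** The planned model is stratified over 150 centers. With 150 strata and conditional HR 0.80, one simulation (300 trials per setting, equal strata) gave relative efficiencies of 1.03, 1.05 and 1.06 at SD 0.6, 0.8 and 1.0. Another (200 trials per setting) gave 1.02-1.10 over the same range, and 1.04-1.10 without strata. The gain survives stratification and may be somewhat smaller.

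**4. Conversion to power.** Power = Φ(3.247 × √RE − 1.960).
- RE 1.02: Φ(3.279 − 1.960) = 90.6%
- RE 1.10: Φ(3.405 − 1.960) = 92.6%

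Against 90.1%, that is a gain of 0.5 to 2.5 points. The table's largest gain at SD 1.0 or below is about 3 points, hence roughly 0.5-3.

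**5. Type I error.** Under HR 1.0 (1500 trials, SD 1.0) it was 5.0% unadjusted and 5.3% adjusted. Both are compatible with 5%.

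**6. Chance imbalance.** The SE of a standardized baseline difference is 2/√12 702 = 0.018. At SD 0.8 it moves the log hazard ratio by 0.8 × 0.018 = 0.014, about a fifth of the SE of 0.069.

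**The case against.** The strongest reply is that nothing here is wrong. The model is prespecified, respects the only randomization stratum, has the right Type I error and matches the sample-size calculation. Choosing a marginal hazard ratio is legitimate. All of this stands, and it is why the point is only a suggestion.

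A second reply is that the gain rests on an assumed score SD. Everyone enrolled is at least 50, has type 2 diabetes and raised systolic BP, and meets a risk criterion, while severe kidney disease is excluded; this narrows the spread of risk. This stands too: at SD 0.5 the gain is only 0.6 points, and gains near 3 points need a strong score (c about 0.75).

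Stronger readings are tempting, and the article does not support them:
- *All baseline information is barred.* Center enters as a stratifying factor, and the sentence governs the primary model. A supportive adjusted analysis may sit in the analysis plan, which is not shown.
- *Adjustment is free.* It changes the target from a marginal to a covariate-conditional hazard ratio, and it needs fixed covariates, functional forms and a rule for missing values.
- *Chance imbalance is a material threat.* At this sample size it is small, and the planned test already allows for it.
- *The trial is underpowered without adjustment.* This does not follow from the section 2.7.1 assumptions if 0.80 is read as the hazard ratio that the planned model estimates. Unadjusted power falls below 90% in the table's last column only because 0.80 is there taken as the conditional ratio.

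What remains is that the article expressly fixes treatment as the only predictor, so this is a stated choice and not a detail left to an unseen document.

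**Conclusion.** The point holds as a minor matter of efficiency. The planned analysis is valid and reaches 90% power on its own assumptions. By using no patient-level prognostic covariate it forgoes about 2-10% relative efficiency, or roughly 0.5-3 points of power.

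The direction is firm. The size depends on the assumed score SD of 0.6-1.0, for which the article offers no figure, and on how much prognostic variation the center strata already absorb. It should rank as an optional improvement, below the changes that the sponsor ought to make.

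**What to change.** Before unblinding, and while the statisticians are still masked (section 2.6), amend the primary analysis as follows:
- Cox model stratified by center, with treatment plus a short prespecified list: age and systolic BP (continuous), sex, previous CVD, eGFR, HbA1c and smoking, each with its functional form stated.
- A simple imputation rule for missing baseline values.
- A statement that the target is the hazard ratio conditional on these covariates.
- The treatment-only, center-stratified model reported as supportive.

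The cost is a dated amendment and some wording; no extra patients, visits or measurements are needed. The downside is small: the headline hazard ratio becomes conditional, so comparison with trials that report unadjusted ratios should use the supportive result. Because 11 927 participants were already enrolled by 30 September 2021 in an open-label trial, the amendment should record that it was made without sight of outcomes by treatment group.

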## QUALITY CONTROL

3

The BPROAD Manual of Procedures (MOP) includes all the details of trial procedures. We use the BPROAD MOP to train study investigators and staff and as a reference during trial preparation and conduct. Key study procedures are standardized, such as standard forms, equipment, and procedures in the study centers for BP measurement, the use of a central laboratory, ECG reading center, and outcome assessment committee at the Coordinating Center.

Training of staff is important to standardize procedures and assure data quality. We organize up to 10 training sessions at different regions across mainland China. Staff members from study centers within the regions are convened in a single, centrally administered face‐to‐face training session. We conduct a second face‐to‐face training at individual study center before screening of the first participant in that study center. Training videos are available for study staff to watch at any time. In addition, the Coordinating Center organizes yearly refresher training sessions to all study centers.

Data are collected using an electronic data capture system. The Coordinating Center is responsible for data monitoring and query reports. Study center staff is responsible for reviewing and resolving the data queries in a timely manner. Routine (eg, monthly) quality control reports will be developed by the Coordinating Center and will be distributed to all study centers on measures of process, impact, and outcomes.

Study samples are collected and centrifuged, aliquoted, and stored at −80 degrees before shipment in dry ice to the central laboratory within 3 months after collection. The central laboratory participates in the American College of Pathologists' Laboratory Accreditation Program and is reviewed and accredited on a regular basis. Samples are measured according to standard procedures and quality control requirements to ensure high‐quality measurement data. Samples that do not undergo measurement are stored at −80 degrees in the Coordinating Center for future research.

## 
BPROAD DURING COVID‐19

4

The first cases of COVID‐19 infection were reported in China in late December 2019. Wuhan, the city most heavily infected, was locked down during 23 January–8 April 2020. This was regarded as the time period when the COVID‐19 epidemic was severe in mainland China. Radical public health measures including quarantine and social distancing were strictly implemented; therefore, in‐person visits of BPROAD participants with their doctors/investigators became unlikely.

On 10 February 2020, the BPROAD Coordinating Center developed an urgent response plan to the outbreak of COVID‐19 according to the China Forums of Clinical Research Capacity Building and Human Research Participants Protection Consensus on Clinical Trial Management under First‐level Response to Major Public Health Emergencies (Infectious Diseases).^17^ The response plan recommended to (a) cancel or suspend all screening, baseline/randomization, and the first yearly visits; (b) collect trial data by telephone interviews at the scheduled date; and (c) complete data collection within 2 weeks of the scheduled date for all BPROAD study centers. BP levels were obtained using home BP monitoring (HBPM). Training and instructions on HBPM were provided to each participants for them to measure and record BP levels at home accurately and report to their doctors/investigators. Medications were adjusted at the discretion of the study physician taking into account the target systolic BP and the validity of BP numbers provided by the participant. The same targets for home BP and clinic BP were recommended. A drug prescription for 90 days on each fill is encouraged by the central government for chronic diseases including hypertension during the outbreak. Although BPROAD in‐person visit is not required, patients can still go to clinics for prescriptions if drug refill is needed. Information on study outcomes and SAEs was asked and supporting clinical materials are obtained afterward whenever possible. The response plan was approved by the IRB of Ruijin Hospital and the DSMB, and was implemented until 31 March 2020.

## STUDY ENROLLMENT

5

BPROAD participants are recruited from diabetes clinics across mainland China. The first BPROAD participant was randomized on 24 February 2019. Participant recruitment was ahead of schedule until the outbreak of COVID‐19 in mainland China in January 2020 (Figure 3), after which participant recruitment was slowed down substantially. By 30 September 2021, a total of 16 047 patients have been screened and 11 927 participants have been enrolled, although the planned completion of recruitment was on 24 February 2021. We anticipate to complete recruitment by the end of 2021.

**FIGURE 3 jdb13411-fig-0003:**
[figure not shown]
Study enrollment till 30 September 2021.

## CONCLUSIONS

6

Previous studies have demonstrated the benefits of BP reduction to <140 mm Hg on lowering the risk of CVD and all‐cause mortality among subjects with or without diabetes.^7^, ^8^ The SPRINT trial revealed additional benefits of further BP reduction to <120 mm Hg among subjects without diabetes.^10^ However, the ACCORD trial failed to support further BP reduction to <120 mm Hg among subjects with diabetes. The less‐than‐anticipated occurrence of major CVD events in the control group might play a part in the null finding.^9^ The appropriate target for systolic BP reduction in patients with diabetes remains uncertain.

The BPROAD study is designed to answer the question whether there are additional cardiovascular benefits to lower systolic BP to <120 mm Hg compared with systolic BP to <140 mm Hg among patients with diabetes over a follow‐up period of up to 5 years with an estimated 90% statistical power. Together with the SPRINT and ACCORD trials (Table 4), as well as other ongoing BP target trials worldwide, the BPROAD study will have essential impacts on public health and clinical practice of BP management.

**TABLE 4 jdb13411-tbl-0004:** ACCORD BP, SPRINT, and BPROAD trials.

	ACCORD BP	SPRINT	BPROAD
Study period	2003–2009	2010–2015	2019~
Study design	Factorial assignment (2‐by‐2)	Parallel assignment	Parallel assignment
Masking	Open label (blinded outcome adjudication committee)	Open label (blinded outcome adjudication committee)	Open label (blinded outcome adjudication committee)
Participants			
Number	4733	9361	12 702 (anticipated)
Country	United States and Canada	United States	China
Age	40 to 79 years	≥50 years	≥50 years
Eligibility criteria	Type 2 diabetes, elevated systolic BP, and increased CVD risk	Elevated systolic BP, and increased CVD risk excluding those with diabetes or previous stroke	Type 2 diabetes, elevated systolic BP, and increased CVD risk
Intervention	Systolic BP <120 mm Hg vs systolic BP <140 mm Hg	Systolic BP <120 mm Hg vs systolic BP <140 mm Hg	Systolic BP <120 mm Hg vs systolic BP <140 mm Hg
Mean intervention duration	4.7 years	3.26 years (median)	4 years (anticipated)
Primary outcome	A composite of nonfatal myocardial infarction, nonfatal stroke, and CVD death	A composite of myocardial infarction, acute coronary syndrome, stroke, acute decompensated heart failure, and CVD death	A composite of non‐fatal stroke, non‐fatal myocardial infarction, hospitalized or treated heart failure, and CVD death

Abbreviations: ACCORD, Action to Control Cardiovascular Risk in Diabetes; BP, blood pressure; BPROAD, Blood Pressure Control Target in Diabetes; CVD, cardiovascular disease; SPRINT, Systolic Blood Pressure Intervention Trial.
